**Reasons for Treatment Discontinuation or Modification and Actions to be Taken**

| Reason for Discontinuation/Modification                                                                                                                                                                         | Action                                                                                                                                                                                                                                                                                                                                                                                                                                                                                                                                                                                       |
|------------------------------------------------------------------------------------------------------------------------------------------------------------------------------------------------------------------------|-----------------------------------------------------------------------------------------------------------------------------------------------------------------------------------------------------------------------------------------------------------------------------------------------------------------------------------------------------------------------------------------------------------------------------------------------------------------------------------------------------------------------------------------------------------------------------------------------------|
| Safety Reason                                                                                                                                                                                                   |                                                                                                                                                                                                                                                                                                                                                                                                                                                                                                                                                                                                     |
| Grade 3 or 4 adverse event/toxicity at least possibly related to telaprevir, except for grade 3 elevations in ALT/AST, grade 3 or 4 GGT elevations, and grade 3 or 4 hemoglobin decreases (unless they are persistent) | 
 
• Permanently discontinue telaprevir and continue Peg-IFN-alfa and RBV.
 
• Permanently discontinue telaprevir and interrupt RBV or RBV and Peg-IFN-alfa if clinically indicated.
 
• Peg-IFN-alfa and/or RBV may be restarted if there is improvement in the adverse event/toxicity within 14 days following the interruption. RBV monotherapy is not allowed.
 
                                                                                                                                                                     |
| Treatment with systemic corticosteroids                                                                                                                                                                                | 
 
• Permanently discontinue telaprevir, Peg-IFN-alfa, and RBV immediately.
 
                                                                                                                                                                                                                                                                                                                                                                                                                                                                          |
| Grade 3 rash (for DRESS, EM, and AGEP, see special instructions below)                                                                                                                                                 | 
 
• Permanently discontinue telaprevir immediately and continue Peg-IFN-alfa and RBV.
 
• Interrupt RBV if the rash does not improve within 7 days after telaprevir discontinuation and continue Peg-IFN-alfa unless interruption is medically indicated. The investigator may also discontinue telaprevir, Peg-IFN-alfa, and RBV simultaneously if clinically indicated.
 
• Peg-IFN-alfa and/or RBV may be restarted if there is improvement in the rash within 14 days following the interruption. RBV monotherapy is not allowed.
 
 |
| DRESS, EM, and AGEP                                                                                                                                                                                                    | 
 
• Permanently discontinue telaprevir, Peg-IFN-alfa, and RBV immediately.
 
                                                                                                                                                                                                                                                                                                                                                                                                                                                                          |
| Grade 4 rash (ie, skin rash that is considered life-threatening), including SJS and TEN                                                                                                                                | 
 
• Permanently discontinue telaprevir, Peg-IFN-alfa, and RBV immediately.
 
                                                                                                                                                                                                                                                                                                                                                                                                                                                                          |
| Anemia (please also refer to Section 9.3.1.2)                                                                                                                                                                          | 
 
• The investigator should consider adjusting the RBV dose, per the product labelling of RBV.
 
• If RBV is permanently discontinued for the management of anemia, telaprevir must also be permanently discontinued.
 
                                                                                                                                                                                                                                                                                                                        |
| Telaprevir safety reason other than the ones specified above a                                                                                                                                              | 
 
• Permanently discontinue telaprevir and continue Peg-IFN-alfa and RBV (regardless of HCV RNA value).
 
                                                                                                                                                                                                                                                                                                                                                                                                                                             |
| Inadequate virologic response                                                                                                                                                                                   |                                                                                                                                                                                                                                                                                                                                                                                                                                                                                                                                                                                                     |
| HCV RNA >100 IU/mL at Week 4                                                                                                                                                                                           | 
 
• Permanently discontinue telaprevir
 
                                                                                                                                                                                                                                                                                                                                                                                                                                                                                                              |
| HCV RNA >100 IU/mL at Week 12                                                                                                                                                                                          | 
 
• Permanently discontinue Peg-IFN-alfa and RBV
 
                                                                                                                                                                                                                                                                                                                                                                                                                                                                                                    |
| HCV RNA levels beyond Week 12                                                                                                                                                                                          | 
 
• Refer to the local prescribing information for Peg-IFN-alfa and RBV
 
                                                                                                                                                                                                                                                                                                                                                                                                                                                                             |

a If in the best interest of the subject according to the investigator

Note: Telaprevir dose modifications are prohibited and once telaprevir treatment is discontinued because of one of the withdrawal criteria specified above, it may not be reinitiated. Dose modifications, interruptions, or discontinuations of Peg-IFN-alfa or RBV should be in accordance with the local prescribing information of Peg-IFN-alfa or RBV, respectively.

AGEP=acute generalized exanthematous pustulosis; ALT=alanine aminotransferase; AST=aspartate aminotransferase; DRESS=drug-related eosinophilia with systemic symptoms; EM=erythema multiforme; GGT=gamma-glutamyltransferase; Peg-IFN=pegylated interferon; RBV=ribavirin; SJS=Stevens-Johnson syndrome; TEN=toxic epidermal necrolysis.

The date and the reason for discontinuation must be noted on the CRF.

If a subject discontinues treatment before the end of the treatment phase, obtain early treatment discontinuation and follow-up assessments, unless informed consent for further follow-up has been withdrawn.

For all subjects, it is recommended that a posttreatment follow-up visit (including sampling for HCV RNA) be performed 24 weeks after the last administered dose of treatment (ie, telaprevir, Peg-IFN-alfa, or RBV) (eg, Week 48 for subjects receiving

24 weeks of treatment, Week 72 for subjects requiring 48 weeks of treatment, 24 weeks after last administered dose of treatment for subjects who discontinue treatment early or withdraw from the open-label treatment phase without withdrawing informed consent).

Subjects who discontinue study drugs prematurely will be instructed to continue the contraception and pregnancy testing procedures outlined in Section 4.3, Prohibitions and Restrictions until 4 months (female subjects of childbearing potential) or 7 months (male subjects and their female partners of childbearing potential) after the last intake of RBV, depending on the local prescribing information.

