For all subjects, stopping rules based on virologic response (ie, HCV RNA levels) will be applied to ensure that telaprevir or Peg-IFN-alfa/RBV treatments are stopped if subjects have viral breakthrough or failure. At Weeks 4 and 12, the stopping rules presented in the table below will be applied. For guidelines for treatment discontinuation after Week 12 of treatment, refer to the local prescribing information for Peg-IFN-alfa and RBV.

| Guidelines for Discontinuation of Telaprevir, Peg-IFN-alfa and RBV Treatment |                                    |                                     |
|------------------------------------------------------------------------------|------------------------------------|-------------------------------------|
| Medicinal product(s)                                                         | > 100 IU/mL at Week 4 of treatment | > 100 IU/mL at Week 12 of treatment |
| Telaprevir                                                                   | Permanently discontinue            | Telaprevir treatment completed      |
| Peg-IFN-alfa/RBV                                                             | Continue to Week 12 decision point | Permanently discontinue             |

Additional plasma HCV RNA levels should be measured at Week 24 for subjects with a total treatment duration of 24 weeks and at Weeks 24 and 48 for subjects with a total

treatment duration of 48 weeks. Additionally, all subjects should have a follow-up visit, including measurement of plasma HCV RNA levels, 24 weeks after the last administered dose of any treatment (ie, telaprevir, Peg-IFN-alfa, or RBV) (eg, Week 48 for subjects receiving 24 weeks of treatment, Week 72 for subjects requiring 48 weeks of treatment).

Subjects who discontinue all treatments (ie, telaprevir, Peg-IFN-alfa, and RBV) early or withdraw early from the early access program should have an early treatment discontinuation/early withdrawal visit performed and a follow-up visit performed 24 weeks after the last administered dose of treatment, unless informed consent for further follow-up has been withdrawn. Plasma HCV RNA levels should be measured at each of these visits.

Recommended evaluations of safety and tolerability to be performed during the early access program are presented in the Time and Events Schedule that follows the Synopsis.

A diagram of the early access program is provided below.

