### **3.2.5. Treatment Modifications Based on Virologic Response**

Evolution of viral population evidenced by an additional gain in mutations is expected if telaprevir dosing is continued in subjects with viral breakthrough (defined as an increase of >1 log HCV RNA compared to the lowest recorded on-treatment value, or if the HCV RNA had become undetectable, a confirmed increase to HCV RNA >100 IU/mL). This was seen in some subjects in Trial 104EU. However, evolution of resistant variants may be limited if telaprevir dosing is stopped after breakthrough is detected, as observed

for some subjects in Trial 104. The majority of breakthroughs (75%) occurred within 4 weeks after the start of telaprevir treatment. These results highlight the importance of closely monitoring subjects and discontinuing telaprevir dosing in case of viral breakthrough or virologic failure.

To ensure that viral breakthrough or failure has not occurred, subjects must have plasma HCV RNA levels monitored throughout the study. Telaprevir should be discontinued if HCV RNA is >100 IU/mL at Week 4. Peg-IFN-alfa/RBV should be discontinued if HCV RNA is >100 IU/mL at Week 12. Beyond Week 12, the guidelines for treatment discontinuation in the local prescribing information for Peg-IFN-alfa and RBV will be followed. The value of 100 IU/mL was selected as it offers good discrimination between subjects who are virologic failures as opposed to those with a slower response to the treatment regimen.

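### Section 10.2 gives conflicting Peg-IFN-alfa/RBV instructions, with no stated precedence, for a subject who stopped telaprevir under the residual safety row and exceeds 100 IU/mL at Week 12

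*Protocol*

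**What the plan says.** The table in Protocol Section 10.2 lists reasons for stopping or modifying treatment, and its lead-in makes the listed actions mandatory. After separate rows for related grade 3 or 4 toxicity, systemic corticosteroids, the rash categories and anemia comes a residual row, "Telaprevir safety reason other than the ones specified above". Its action is to stop telaprevir permanently and "continue Peg-IFN-alfa and RBV (regardless of HCV RNA value". A footnote to the row adds only "If in the best interest of the subject according to the investigator".

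Further down, the row for HCV RNA above 100 IU/mL at Week 12 says "Permanently discontinue Peg-IFN-alfa and RBV".

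Section 3.1 sets the scope of the virologic rules: "For all subjects, stopping rules based on virologic response (ie, HCV RNA levels) will be applied", and "At Weeks 4 and 12, the stopping rules presented in the table below will be applied". Its table says of Peg-IFN-alfa/RBV, when HCV RNA exceeds 100 IU/mL at Week 4, "Continue to Week 12 decision point"; above the same threshold at Week 12 both drugs are stopped permanently. Section 3.2.5 repeats the rule: "Peg-IFN-alfa/RBV should be discontinued if HCV RNA is >100 IU/mL at Week 12". The Synopsis, footnote d of the Time and Events Schedule and the Definition of Terms give the same Week 12 rule. None of these places exempts a subject who stopped telaprevir for safety.

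**The concern.** Two rows of one mandatory table can apply to the same subject at the same visit and point in opposite directions. One site may read the HCV RNA parenthetical as a deliberate exemption from the Week 12 rule; another may apply the Week 12 rule because it is stated for everyone. Neither would be plainly departing from the protocol.

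The consequence is different Peg-IFN-alfa/RBV exposure, by site, in subjects who have already had a safety problem on telaprevir. Their visit schedule and their contribution to the HCV RNA summaries would also depend on how the site read the table.

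**Working it through.** No sample size, power or error rate is involved, and the 100 IU/mL threshold is the same wherever it appears. The check is a comparison of the rules, followed by simple arithmetic on what is at stake.

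**Where the rules agree and where they do not.** Take a subject who stops telaprevir before Week 12 under the residual row.

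| HCV RNA result | Residual safety row | Virologic rule | Agreement |
|---|---|---|---|
| Above 100 IU/mL at Week 4 | Continue Peg-IFN-alfa/RBV | Continue to Week 12 | Yes |
| At or below 100 IU/mL at Week 12 | Continue | Stopping rule not triggered | Yes |
| Above 100 IU/mL at Week 12 | Continue whatever the value | Stop permanently | No |

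The conflict is confined to the third line.

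**Does anything in the text settle it?**
- The residual-row footnote brings in investigator judgement but does not mention the Week 12 rule.
- The note under the table refers Peg-IFN-alfa/RBV changes to local prescribing information. That adds another authority without ranking it.
- The rows for related grade 3 or 4 toxicity and for grade 3 rash also allow Peg-IFN-alfa/RBV to continue, but without the HCV RNA parenthetical. They do not claim to override the virologic rules.

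**Exposure at stake.** A subject above 100 IU/mL at Week 12 has detectable virus, so under Section 3.1 the planned total for any subject type is 48 weeks if treatment is not stopped. The disputed period is 48 − 12 = 36 weeks. This is an outer bound, because after Week 12 local prescribing information may lead to an earlier stop.

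**Visit schedule.** Follow-up is 24 weeks after the last dose. A subject stopped at Week 12 has it at 12 + 24 = Week 36; one who completes 48 weeks has it at 48 + 24 = Week 72, with HCV RNA also measured at Weeks 24 and 48. The reading therefore determines which of the descriptive summaries in Section 11.3 the subject enters.

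**Adverse event window.** Section 12.3.1 limits routine CRF recording to 30 days after the last telaprevir dose. Week 12 is day 84. A subject who stopped telaprevir before day 84 − 30 = 54 has no overlap between that window and the disputed period. One who stopped later has at most 30 days of overlap.

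**Number of subjects.** The protocol gives no rate for telaprevir safety stops, for the share falling in the residual row, or for HCV RNA above 100 IU/mL at Week 12 among them. For scale only, assume that 5% to 15% of 3,000 subjects stop telaprevir for any safety reason before Week 12, and that 10% to 30% of those exceed the threshold:
- low: 3,000 × 0.05 × 0.10 = 15
- high: 3,000 × 0.15 × 0.30 = 135

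That range counts all safety stops. If, again as an assumption, 10% to 30% of them fall in the residual row:
- low: 15 × 0.10 = 1.5
- high: 135 × 0.30 = 40.5

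The result is roughly 2 to 40 subjects.

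**The case against.** The best defence is that the rows act in sequence. The residual row would govern the moment telaprevir stops and mean only that the HCV RNA value at that moment is no reason to stop the other two drugs; the Week 12 decision would follow as usual. This matches the Week 4 rule, and the Week 12 rule is repeated so often that one parenthetical is a thin basis for an exemption.

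The reading is plausible, but the protocol does not state it. It also leaves the parenthetical with almost nothing to do: no virologic rule in the protocol stops Peg-IFN-alfa/RBV before Week 12, so there is no earlier rule to set aside. The words acquire real effect only from Week 12, where they collide with the other row.

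Several limits do stand. A reader might infer that every telaprevir safety stop is affected, but the wording is confined to the residual row. A reader might infer that sites are compelled to continue treatment, but the footnote leaves room for judgement. A reader might infer damage to the safety dataset, but most of the disputed period lies outside the adverse event window, although later serious events reported spontaneously must still go on the serious adverse event form. Finally, the CRF already captures the date and reason for discontinuation (Section 10.2) and the start and stop dates of hepatitis C therapy (Section 8), so divergent handling would be partly visible afterwards.

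**Conclusion.** The point holds in a narrow form. For a subject who stopped telaprevir under the residual, investigator-judged row and has HCV RNA above 100 IU/mL at Week 12, the protocol gives conflicting Peg-IFN-alfa/RBV instructions and no order of precedence. That conclusion rests on the text alone.

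The number affected cannot be derived from the protocol. It is a subset of all safety stops and so probably well below the 15 to 135 shown for scale; every rate behind those figures and the narrower range is an assumption. The consequences are inconsistent Peg-IFN-alfa/RBV exposure across sites and inconsistent descriptive HCV RNA percentages for these subjects. With no hypothesis tested and no formal efficacy analysis, no inferential result is at risk. The point merits correction because it concerns a stopping instruction that sites must follow.

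**What to change.** Reconcile the residual safety row in Section 10.2 with the Week 12 row of that table, the Synopsis, footnote d of the Time and Events Schedule, the Definition of Terms, and Sections 3.1 and 3.2.5. One rule should say whether the Week 12 virologic rule applies after a residual telaprevir safety stop. If it does, delete the parenthetical or limit it in time; if it does not, state the exception wherever the rule is given. Which rule is clinically right is for the sponsor's clinicians to decide.

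The cost is small: a short amendment centred on one table row, with matching wording elsewhere if an exception is kept, and a clarification letter to sites. No new data collection is needed.
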